### Statistical analysis

The data will be analyzed in the latest version of the R Studio program. A statistical analysis will be performed based on the purposive analysis principles. The assumption of normality for the quantitative variables will be verified with the Shapiro–Wilk test, followed by a descriptive analysis; for the continuous variables, measures of central tendency or dispersion according to the data will be applied. For categorical variables, the proportions and frequencies will be calculated. Differences between the groups in measurements for the primary and secondary objectives will be analyzed by repeated measures ANOVA the variables with a normal distribution. Nonparametric tests will be performed if the data do not comply with the assumption of normality, interaction of arm by time effect will not be tested. Qualitative variables will be evaluated with the chi-square test of independence or Fisher’s exact test, as appropriate. For all tests, a significance level of p <0.05 will be employed.

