#### Discontinuation of participation

During the course of the study, any participant can choose to withdraw from the trial at any time. Participants can choose to suspend treatment and/or evaluations in the study but can remain in the follow-up if they wish; however, participants can also withdraw their consent, which implies that they wish to completely withdraw from the study, completely restricting the researchers’ access to the data obtained to date and those participants’ clinical histories.

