### Outcomes

The primary outcome will be joint mobility measured by the Bath Ankylosing Spondylitis Metrology Index (BASMI). The secondary outcomes will be the Bath Ankylosing Spondylitis Functional Index (BASFI), Bath Ankylosing Spondylitis Disease Activity Index (BASDAI), and the Ankylosing Spondylitis Quality of Life Questionnaire (AsQol) [27, 28]. Each of these variables will be measured before the intervention, after the intervention, and four weeks after the intervention. The participants will undergo an initial evaluation before randomization. The results will be collected at each time point according to (Figs 1 and 2).

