### Sample size

The sample size was calculated in the program R Studio version 3.5.3, package of superiority clinical trials, based on a mean difference of 4.0 in the BASMI with a standard deviation of 2, an r (ratio) between groups of 1, and assuming a loss of 20%. An alpha one sided of 0.05% and a power of 0.80 were estimated based on mean difference test corresponding to a clinical trial of superiority (repeated measures ANOVA). The total number of people was 82 (42 per arm). Non probabilistic purposive sampling will be used.

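### The analysis population is named by an undefined term, and repeated measures ANOVA in its classical form would exclude participants with a missed visit

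*Protocol article*

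**What the plan says.** On who is analysed, the Statistical analysis section has one sentence: "A statistical analysis will be performed based on the purposive analysis principles". The only other use of the adjective is in the Sample size section and concerns recruitment: "Non probabilistic purposive sampling will be used". The article does not mention intention to treat, per protocol or complete cases.

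On method, the same section says: "Differences between the groups in measurements for the primary and secondary objectives will be analyzed by repeated measures ANOVA the variables with a normal distribution". Unnamed nonparametric tests are the fallback if normality fails.

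On visits, the Outcomes section says: "Each of these variables will be measured before the intervention, after the intervention, and four weeks after the intervention". That makes three values per participant for the BASMI and for each secondary outcome.

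On loss, the Sample size section works with "an r (ratio) between groups of 1, and assuming a loss of 20" per cent. The Discontinuation of participation section lets people stop treatment or evaluations and still remain in follow-up. Someone who withdraws consent altogether removes the researchers' "access to the data obtained to date".

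**The concern.** In a superiority trial the analysis population decides which randomised people count. Here the sentence that should settle this uses a term that belongs to sampling. A reader cannot tell from it whether everyone randomised is analysed as allocated, and different sets could later be claimed to fit it.

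The choice of method makes this matter. Classical repeated measures ANOVA needs a complete row of data. A participant seen at baseline and after treatment, but missing at the four-week visit, drops out of the whole analysis, including the post-treatment comparison to which they could contribute. The exclusion happens after randomisation. If staying in the trial depends on how a participant responds, and does so differently by arm, the completers are no longer comparable groups.

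**Working it through.** **Inputs.** From the article: 84 randomised (Abstract; 42 per arm in Sample size, which also prints a total of 82), loss 20%, BASMI SD 2, planned difference 4.0, power 0.80, three visits. Assumed here because the article gives no figure: the correlation between baseline and post-treatment BASMI, the pattern of loss, and a true effect of 1.0 point.

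**1. How many could be excluded.** 84 × 0.20 = 16.8, so about 17 excluded and 84 × 0.80 = 67.2, about 67, complete. From 82 the figures are 16.4 and 65.6. This takes 20% as the share with any missed visit. If instead 20% were missing independently at each of the two post-baseline visits, 0.8 × 0.8 = 64% would be complete, about 54 of 84.

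**2. Power.** The printed total of 82 (or 84) does not reproduce from its inputs. With n per arm = 2(z_α + z_β)² SD²/δ², one-sided 0.05 gives 2 × (1.645 + 0.842)² × 4/16 = 3.1, so 4 per arm, or 5 after inflation for loss. That is a separate matter, but it bears on this point. With 33 completers per arm, the standardised difference is 4/(2√(2/33)) = 8.12. Power is Φ(8.12 − 1.645) at one-sided 0.05, and Φ(8.12 − 3.29) if the printed alpha of 0.05% is taken literally. Both exceed 0.999, so exclusion does not threaten power for the stated effect.

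**3. Precision.** If all the loss fell after the post-treatment visit, dropping those people would inflate the standard error of the post-treatment contrast by √(84/67) = 1.12. The article does not name that visit as the primary time point, so this is an illustration.

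**4. Bias.** Simulated with 42 per arm, SD 2 and a true benefit of 1.0. The entries are the mean benefit estimated from completers.

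| Loss pattern (sham / active) | Correlation | Measure | Estimate |
|---|---|---|---|
| Random 20% / random 20% | 0.8 | change | about 1.0 |
| Random 30% / random 10% | 0.8 | change | about 1.0 |
| Worst-changing 20% / worst-changing 20% | 0.8 | change | 1.00 |
| Worst-changing 20% / random 20% | 0.9 | change | 0.71 |
| Worst-changing 30% / random 10% | 0.8 | post-treatment mean | 0.69 |
| Worst-changing 20% / random 20% | 0.8 | change | 0.59 |
| Worst-changing 30% / random 10% | 0.9 | change | 0.55 |
| Worst-changing 20% / random 20% | 0.6 | change | 0.43 |
| Worst-changing 30% / random 10% | 0.8 | change | 0.37 |

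A hand check of the last row: the SD of change is 2√(2(1 − 0.8)) = 1.265. Cutting the worst 30% of a normal distribution moves the mean of the rest by φ(0.524)/0.7 = 0.497 SD. The shift is 0.497 × 1.265 = 0.63, and 1.0 − 0.63 = 0.37.

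The selective rows span roughly 0.4 to 0.7, but these are not bounds. The last pattern at correlation 0.6 gives 1.0 − 0.497 × 2√0.8 = 0.11, and milder patterns give values closer to 1.0.

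**5. A second route.** Suppose the 20% lost in one arm differ from that arm's completers by 0.25 to 1.0 SD. The between-arm difference then moves by 0.2 × (0.25 to 1.0) × 2 = 0.1 to 0.4 points. With opposite shifts in the two arms it moves by 0.2 to 0.8.

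**The case against.** **It may be only a translation slip.** The English shows other signs of translation: adverse events appear under the heading Damage, and the Discussion speaks of hard declines where outcomes seem to be meant. Intention to treat is a plausible original. That stands as an explanation, but nothing in the article confirms it, so the sentence still needs correcting.

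**Exclusion is inferred.** A reader might conclude that the plan drops everyone with a missed visit. The article does not say so. That is the usual behaviour of the classical method, some R implementations keep partial data, and a rule for missed visits may sit in an analysis plan that is not shown. Silence on missing data is therefore not counted as a fault here. The stated method is, because a better one is available at little cost.

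**Loss need not bias.** A reader might also infer that 20% loss breaks the randomised comparison. The documents do not support that. The 20% is a planning allowance, participants are to be blinded by a visually matched sham, and the whole course is short. Random or symmetric loss leaves the estimate intact, and the 0.37 figure is one severe scenario.

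**The withdrawal rule.** It is tempting to read the Discontinuation of participation section as a further breach of intention to treat. It is weaker than that. Follow-up after stopping treatment is expressly allowed, and loss of earlier data is confined to full withdrawal of consent. That is a consent and ethics matter, the number affected is unknown, and no model can recover data that may not be used.

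**Conclusion.** The point holds in two linked parts. First, the analysis population is stated in a term that is undefined and not recognised, which is a fault of the printed text whatever its origin. Second, the named method, in its classical form, would exclude about 17 of 84 randomised participants at the plan's own loss rate, when a method that keeps their observed visits is readily available.

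The consequence is wasted data and a risk of bias, conditional on loss being related to arm and outcome. Its size ranges from nothing to an estimate of roughly 0.4 to 0.7 for a true 1.0 in the selective scenarios shown. Those figures rest on an assumed effect, assumed correlations of 0.6 to 0.9 and assumed patterns of loss. Only the SD and the 20% come from the article. Other patterns of selective loss could exaggerate a benefit instead of hiding one.

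**What to change.** In the Statistical analysis section:

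- Replace the sentence on the analysis principle with: *All randomised participants are analysed in the arm to which they were allocated (intention to treat).*
- Replace repeated measures ANOVA with a likelihood-based mixed model for repeated measures that uses every available visit. A participant missing only the four-week visit then still contributes baseline and post-treatment values.
- Add one sensitivity analysis for data missing not at random. The mixed model assumes that loss is explained by what has been observed, and it cannot itself correct loss that depends on unseen values.

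The sample size, visits and treatment stay as they are. The cost is a few lines of wording and slightly more analysis work. No change to the consent-withdrawal wording is required for this point.

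### A Shapiro–Wilk test on the outcome values, not on model residuals, decides whether the primary BASMI comparison is repeated measures ANOVA or an unnamed nonparametric test

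*Protocol article*

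**What the plan says.** All of this is in the Statistical analysis section of the protocol article.

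- The check: "The assumption of normality for the quantitative variables will be verified with the Shapiro–Wilk test".
- The parametric branch, for the primary and the secondary objectives: differences between groups "will be analyzed by repeated measures ANOVA the variables with a normal distribution".
- The other branch: "Nonparametric tests will be performed if the data do not comply with the assumption of normality". No test, visit or handling of baseline is named.
- The same sentence continues: "interaction of arm by time effect will not be tested". It is unclear whether this covers both branches or only the nonparametric one.
- The level: "For all tests, a significance level of p <0.05 will be employed". Presumably this covers the Shapiro–Wilk tests too.

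Under Outcomes, BASMI is primary and BASFI, BASDAI and AsQoL are secondary, each "measured before the intervention, after the intervention, and four weeks after the intervention". The Sample size section rests on a mean difference in BASMI and refers to repeated measures ANOVA. It does not mention a nonparametric route.

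**The concern.** Three features of the rule cause trouble.

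- **Target.** Normality in ANOVA concerns the residuals. The rule tests the variables. By the article's own descriptions these are limited scores: BASMI is scored from an 11-point table, BASFI is an average of items scored 0 to 10, BASDAI comes from 10 cm scales, and AsQoL is a whole number from 0 to 18. Such scores can fail Shapiro–Wilk without harming a comparison of means.
- **Timing.** The primary test is fixed only once outcome data have been tested. The rule does not say whether normality is judged by visit, by arm or overall, or what follows if one visit passes and another fails.
- **Estimand.** The trial is sized on a mean difference. The usual rank tests neither test nor estimate that quantity, so the two branches answer different questions.

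At stake is whether the primary result can be read as the answer to a question fixed in advance.

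**Working it through.** **Inputs from the documents.** Difference 4.0, SD 2, 1:1 allocation, 42 per arm, 20% loss (Sample size); three measurement times (Outcomes). Evaluable per arm: 42 × 0.80 = 33.6, so 33 or 34.

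**Assumed, because the documents give no figure.** Within-person correlation ρ from 0.5 to 0.9, equal between all visits; a smaller true difference of 1.0, to show where methods separate; two-sided 0.05 testing.

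**1. The plan's own figure.** n per arm = 2(z_α + z_β)²(SD/difference)². At one-sided 0.05 and power 0.80 this is 2 × (1.645 + 0.842)² × (2/4)² = 3.1, so 4 per arm, 8 in total and 10 after 20% loss. The stated 82 (42 per arm) is not reproduced. A difference of about 1.2 would be needed. That is a separate matter, but it shows why effects well below 4.0 are worth examining.

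**2. How often the gate trips.** For independent 5% tests on normal data, P(at least one rejects) = 1 − 0.95^k, which is 14% for k = 3 and 26% for k = 6. Simulation with correlated visits gives:

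| Data (assumed) | What is tested | At least one rejection |
|---|---|---|
| Exactly normal | 3 visits, arms pooled | 12–17% |
| Exactly normal | 6 arm-by-visit cells | 25% |
| Moderately skewed (gamma, shape 4) | 3 visits, arms pooled | 88–95% |
| Mean 3, SD 2, steps of 0.2, bounded at 0 | 6 arm-by-visit cells | 61% |

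In the first row, the 16–17% values arise at a true difference of 4.0 and the 12–15% values at differences of 0 to 1.4. Pooled raw values mix two arms with different means, so the treatment effect itself can register as non-normality. Residuals do not have this problem.

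**3. Whether the mean comparison needs protecting.** On the bounded score, baseline-adjusted ANCOVA had a type I error of 5.2%.

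**4. Power at the protocol's difference of 4.0.** SE of a post-treatment difference = 2 × √(2/33) = 0.492, and 4/0.492 = 8.1. Power is about 1.00, and simulation gives about 1.00 for every method compared.

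**5. Power at an assumed difference of 1.0.** Simulated, 33 per arm, normal data:

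| Analysis | ρ = 0.5 | ρ = 0.8 | ρ = 0.9 |
|---|---|---|---|
| Repeated measures ANOVA, arm main effect, no interaction | 0.39 | 0.30 | 0.30 |
| t-test, post values | 0.53 | 0.50 | 0.50 |
| Mann–Whitney, post values | 0.50 | 0.49 | 0.48 |
| t-test, change | 0.50 | 0.89 | 0.995 |
| Mann–Whitney, change | 0.48 | 0.87 | 0.99 |
| ANCOVA | 0.63–0.66 | 0.92 | 1.00 |

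Hand check for ANCOVA: SE = 0.492 × √(1 − ρ²) = 0.426, 0.295 and 0.215. Power = Φ(1/SE − 1.96) = 0.65, 0.92 and 1.00.

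Hand check for the ANOVA main effect: averaging over three visits, one of them baseline, shrinks the effect to 2/3. SE = 0.492 × √((1 + 2ρ)/3) = 0.402, 0.458 and 0.476. Power is about 0.38, 0.31 and 0.29.

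**6. Like for like.** Mean-based against rank-based power is 0.53 against 0.50 on post values (ρ = 0.5) and 0.89 against 0.87 on change (ρ = 0.8). With skewed data and ρ = 0.8 the rank test was slightly ahead: 0.57 against 0.53 on post values and 0.90 against 0.88 on change.

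**The case against.** The rule is written down in advance, and the Blinding section gives the analysis to someone outside intervention and evaluation. A journal article may leave the name of the nonparametric test, its visit and its use of baseline to a full plan. Rank tests lose little and can gain on skewed data. The rejection rates above depend on how the unstated check is carried out.

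Much of this stands. The missing test name alone would not be a finding, and the rates are illustrations under stated readings. But the gate itself is stated, and an analysis plan that follows this article would have to keep it. An independent analyst does not change the fact that outcome data select the method.

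A reader might infer that falling back to ranks halves the power, from 0.92 to 0.49 at ρ = 0.8. The documents do not support that. ANCOVA is the remedy proposed here, not the plan's method. If the no-interaction clause governs the ANOVA, that ANOVA has less power (0.30) than Mann–Whitney on post values (0.49). If the clause governs only the nonparametric branch, the ANOVA could use change over time and a halving becomes possible. It would still need a true difference far below 4.0, a correlation of about 0.8 or more, and a fallback that ignores baseline. Nor does the fallback remove baseline adjustment, because neither branch has any.

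**Conclusion.** The point holds as a flaw in the decision rule. A normality test on the outcome values, rather than on residuals, chooses the primary test of BASMI and of the secondary indices. One of its branches need not estimate the mean difference used for sizing. Under the readings examined, the gate would trip in 12–25% of trials with perfectly normal data and in most trials with skewed or bounded scores, while a mean comparison with about 34 per arm does not need the protection. This conclusion does not rest on any power figure.

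No loss of power against the plan's own ANOVA is claimed, and no inflation of type I error by the two-stage procedure, which was not calculated. What can be said is conditional. At an assumed true difference of 1.0, a baseline-adjusted analysis has power of about 0.63–0.66, 0.92 and 1.00 at correlations 0.5, 0.8 and 0.9. A rank test on post values that ignores baseline has about 0.5 throughout. At the protocol's 4.0 nothing separates the methods.

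**What to change.** - Delete the normality gate. A Shapiro–Wilk result may be reported as description but should select nothing.
- Prespecify one baseline-adjusted ANCOVA or mixed model for BASMI as the primary analysis. The estimate is the arm difference in means, with its confidence interval, at one named visit (end of treatment or four weeks later, as the team decides).
- Use the same model for BASFI, BASDAI and AsQoL, whatever their distribution.
- Check residuals by plots.
- Name one sensitivity analysis: robust standard errors, a bootstrap interval or rank ANCOVA. It does not replace the primary result.

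The baseline measurement is already planned, so no participants or visits are added. The cost is analysis wording and one extra sensitivity analysis.

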### Hypothesis

The myofascial induction group will have better results than the simulation group with respect to joint mobility among people with AxSpA.

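### With the arm-by-time test excluded and no baseline adjustment named, the primary comparison averages the pre-randomization visit into the treatment effect: a valid but diluted and inefficient test

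*Protocol article*

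**What the plan says.** Three parts of the protocol article bear on this point.

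- **Outcomes.** "Each of these variables will be measured before the intervention, after the intervention, and four weeks after the intervention". The first of these precedes allocation: "The participants will undergo an initial evaluation before randomization".
- **Statistical analysis.** "Differences between the groups in measurements for the primary and secondary objectives will be analyzed by repeated measures ANOVA", for variables that are normally distributed. The sentence that provides nonparametric tests as the fallback ends with "interaction of arm by time effect will not be tested". The section names no baseline covariate, change score, follow-up-only model or primary time point.
- **Hypothesis.** "The myofascial induction group will have better results than the simulation group with respect to joint mobility among people with AxSpA".

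The Sample size section also names repeated measures ANOVA, and its calculation is "based on a mean difference of 4.0 in the BASMI with a standard deviation of 2".

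**The concern.** When the pre-treatment value is one level of the time factor, the treatment effect in a repeated measures ANOVA appears as a difference between arms in change, which is an arm-by-time contrast. If that contrast is excluded, the arm main effect is the only between-arm term left. It compares the arms on the mean of three visits, and at one of those visits randomization makes the expected difference zero.

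This has three consequences:

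- the reported effect is shrunk towards zero;
- any chance baseline difference enters the estimate directly;
- the standard error keeps the between-patient variance that baseline adjustment would remove.

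This is more than a detail left for an analysis plan. The exclusion is an explicit statement, and it governs the primary efficacy comparison.

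**Working it through.** **Inputs from the document.** Difference 4.0, SD 2, 42 per arm, 20% loss, three visits (one before randomization), significance at p < 0.05. Analysed per arm: 42 × 0.8 = 33.6, taken as 34.

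**Assumptions, not in the document.** Two-sided testing, equal correlation r between any two visits (range 0.6 to 0.9), equal SD at each visit, normal approximation. The true benefit d is 0 at baseline and the same at both follow-ups. Because the power results depend heavily on d, it is varied as well as r.

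**The plan's own figure.** The stated sample size cannot anchor d. With 4.0 and SD 2, n per arm = 2 × (1.645 + 0.842)² × 2² / 4.0² = 3.1, so 4 per arm at one-sided 0.05, or 5 after 20% loss. At the printed one-sided 0.05% it is 9, or 12 after loss. Neither gives 42. That is a separate matter; here it means that power has to be shown over a range of d.

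**Step 1: what the main effect estimates.** Expected arm difference = (0 + d + d)/3 = 2d/3. At the protocol's 4.0 this is 2.67.

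**Step 2: precision.** The standard error is √(2V/34), with

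- main effect: V = SD²(1 + 2r)/3;
- arm difference in change (mean follow-up minus baseline): V = SD²[(1 + r)/2 + 1 − 2r];
- ANCOVA on the mean of both follow-ups: V = SD²[(1 + r)/2 − r²].

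At r = 0.8 the variances are 3.467, 1.200 and 1.040, and the standard errors are 0.452, 0.266 and 0.247.

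**Step 3: power.** Power ≈ Φ(effect/SE − 1.96). At r = 0.8 and d = 1.0:

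- main effect: 0.667/0.452 = 1.48, power 31%;
- change contrast: 1.0/0.266 = 3.76, power 96%;
- ANCOVA: 1.0/0.247 = 4.04, power 98%.

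Over r = 0.6 to 0.9:

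| True d | Main effect | ANCOVA, mean of both follow-ups |
|---|---|---|
| 4.0 | about 100% | about 100% |
| 2.0 | 81–89% | about 100% |
| 1.5 | 57–67% | over 99% |
| 1.0 | 30–36% | 87–100% |

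Higher correlation lowers power for the main effect and raises it for ANCOVA. A simulation of 5,000 trials at r = 0.8 and d = 1.2 gave a mean main-effect estimate of 0.80 in size (2/3 × 1.2 = 0.80), with power 42% against 98% for the two-degree-of-freedom interaction test.

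**Step 4: chance imbalance, no treatment effect, r = 0.8.** The standard error of the baseline difference is √(2 × 4/34) = 0.485, so a gap of 2 standard errors is 0.97 points. Given that gap, the expected three-visit difference is 0.97 × (1 + 1.6)/3 = 0.841. The conditional variance per subject mean is 3.467 − 3.467²/4 = 0.462, so the conditional SE is √(2 × 0.462/34) = 0.165. The test rejects above 1.96 × 0.452 = 0.885. The probability is 1 − Φ((0.885 − 0.841)/0.165) = 1 − Φ(0.27), about 39%. A gap at least this large in either direction arises in about 5% of trials.

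**The case against.** A reader might infer that the planned ANOVA does not test the hypothesis or cannot answer the primary objective. The documents do not support that. Baseline is measured before randomization, so with no treatment effect the arm main effect has expectation zero and its unconditional type I error is about 5%. A real benefit moves it in the right direction, at two thirds of its size. Nor is the 39% an inflated error rate: it is conditional on an imbalance that few trials will show.

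A reader might also infer that the trial is underpowered whatever the effect. At the protocol's own difference of 4.0, every test considered has power near 100%, and the harm there is the shrunken estimate. The power loss becomes serious only if the true effect is well below 4.0, and the document gives no such smaller value.

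Two readings would soften the problem. The text does not say in words that baseline is a level of the time factor; if the ANOVA covered only the two follow-ups, its arm main effect would be a proper treatment comparison. The exclusion also shares a sentence with the nonparametric fallback and might be limited to it. Neither reading is stated. Three measurements feed an unqualified repeated measures ANOVA, no other use of baseline is given, and no arm-by-time test is provided anywhere else.

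One further objection stands. ANCOVA on the follow-up mean is itself an arm effect without an interaction test. The fault therefore lies in treating baseline as an unadjusted outcome level while excluding the contrast that would isolate change. The missing interaction test alone is not the defect.

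**Conclusion.** The point holds in this form. As most naturally read, the Statistical analysis section makes the primary comparison an arm difference averaged over baseline and both follow-ups. The test is valid, but its estimate is one third too small for a sustained effect, is exposed to chance baseline imbalance, and is less precise than the same data allow. The one-third dilution follows from the visit schedule and does not depend on the SD or the correlation. The power figures rest on SD 2, 34 analysed per arm, two-sided 0.05 and an assumed correlation of 0.6 to 0.9, and they matter in practice only for effects well below 4.0. The conclusion also depends on the two unstated readings not being what was meant. If either was meant, the text needs to say so.

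**What to change.** Delete the clause that excludes the interaction. Deletion alone is not enough, because it names no contrast. State that baseline BASMI enters as a covariate and not as an outcome level, in an ANCOVA or linear mixed model of the follow-up values with arm, visit, arm-by-visit and baseline. Alternatively, test the arm difference in change from baseline, which targets the same effect with somewhat less precision. Prespecify one primary contrast; whether that is the immediate post-treatment visit, the four-week visit or the mean of both is the sponsor's choice, to be made before data are seen. Use the same model for BASFI, BASDAI and AsQoL.

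The cost is analysis wording only. Every measurement needed is already scheduled, and recruitment, visits and sample size are unaffected.
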